### 4.2 Exclusion Criteria

To be eligible for the study participants must not:

- Have a personal history of the following neurological disorders: Alzheimer’s, Amyotrophic Lateral Sclerosis, Multiple Sclerosis, Parkinson’s, Stroke
- Have a personal history of the following cardiorespiratory disorders: Congestive heart failure, Heart attack in past 24 months
- Have a personal history of the following musculoskeletal disorders: Rheumatoid Arthritis, pathologic fractures of the spine, avascular necrosis or osteonecrosis, severe osteoarthritis. Including a history of spine surgery or a hip arthroplasty
- Have active cancer
- Be Blind
- Have used narcotics or muscle relaxants within 30 days prior to study enrollment.
- Report being pregnant, lactating, or that they anticipate becoming pregnant in the next 3-months
- Have a body mass index greater than 35 kg/m^2
- Have clinical depression (i.e., subjects who score 24 or higher on the Center for Epidemiology Depression Scale).
- Report unexplained weight loss over the past month ( $>10$  lbs).

- Report they have pending litigation related to an episode of LBP or are receiving any type of disability services related to low back pain.
- Report having received any manual therapy intervention applied to the spine 30 days prior to first study intervention.
- Current drug or alcohol use or dependence that, in the opinion of the PIs, would interfere with adherence to study requirements.
- Applies to Experiment 3 (Cortical Effects) only: Have a personal or family history of epilepsy or seizures, Migraine Headaches within 6 months (186 days) of V2 physiologic testing, or taking medications in the benzodiazepine class.
- Applies to Experiments 1 and 3 (Muscular Effects and Cortical Effects) only: Have contraindications for exposure to a magnetic field.
- Applies to Experiment 1 (Muscular Effects) only: Have a positive result from pregnancy test administered the day of each MRI.

The supplemental research will enroll an additional 60 healthy participants with no history of LBP and who are matched on sex, age ( $\pm 3$  years), height ( $\pm 2$  inches), and weight ( $\pm 10$  lbs) to the participants recruited into **Experiment 2** of the RELIEF study. The same exclusion criteria are applied to the control group as is used for the RELIEF study LBP participants.

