### Baseline Assessments

The following baseline clinical outcomes and evaluations will be obtained from all study participants, regardless of which treatment arm they are assigned to:

- Numerical Pain Rating (NPR): This scale will quantify the study candidates rating of their low back pain symptoms (see appendix).
- Roland Morris Disability Questionnaire: This form quantifies the self-reported level of disability (see appendix).
- PROMIS Pain Measures: The NIH PROMIS system will be used to assess outcomes related to pain intensity, pain interference, pain behavior, and physical function.
- Prior & Concomitant Medication Form: This form documents the study participant's recent and current medication usage for their low back pain (see appendix).
- Change in Medication Use: This form documents any changes in medication use not related to low back pain.

The following baseline physiological outcomes will be obtained based the experimental group to which they are randomly assigned to (i.e., muscular, spinal, cortical):

- Group 1 (Muscular Effects):
  - Skeletal muscle proton transverse relaxation time (T2) of the lumbar muscles.
    - Location & Assessment Team: Data will be collected at the Ohio Musculoskeletal and Neurological Institutes Biomedical Imaging Suite located in Irvine Hall at Ohio University. Blinded members of The RELIEF Study Team (i.e., blinded students, staff, and the principal investigators) will be involved with the data collection and analysis.
    - Methods: Female participants will be screened for pregnancy using a urine pregnancy test; positive results will exclude a participant from remaining in the study. Data will be collected and analyzed as we have previously

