### 7.1 Specification of Safety Parameters

At visits 2-9 the study staff will use the Health Status Reassessment CRF to ask the study participants if they have had any change in general health since the last visit. If fever or unexplained weight loss is reported, suggesting systemic infection / disease may be causing their low back pain, the clinician will do a basic physical exam and specifically assess for the possibility they have other systemic illness. They will be advised to seek medical care and research participation may be delayed, temporarily discontinued, or permanently suspended at the discretion of the examining clinician and in consultation with the Medical Directors if needed.

Before each treatment the study staff will use the Contraindications for Intervention CRF to inquire about change in back related signs indicative of increased severity of symptoms. Specifically if they have any increases in 1) radiating pain (i.e., burning, numbness, tingling sensations into the legs), 2) have noticed any muscle weakness in the legs, and 3) have any episodes of incontinence of bowel or bladder. If the study participant reports yes on any of these items the clinician will do a basic physical exam and assess neurological function by checking

myotomes, dermatomes, and reflexes to determine whether the study participant now presents with hard neurological signs (e.g., loss of motor function, significant changes in reflexes), or symptoms of other systemic disease. If the participant does present with hard neurological signs or serious systemic disease, they will be encouraged to seek consultation with their personal physician, and they will be excluded from further participation from the study.

Before each experimental measurement lab testing session (Visits 2, 8, and 9) the study staff will use the Contraindications for Lab Testing CRF to inquire specifically about symptoms of health issues contraindicated for the allocated experimental measurement lab test. Migraine headache will be assessed using The ID Migraine™ self-administered screener. If a possible contraindication is identified the PIs are consulted to determine safety before the lab testing begins.

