## 8. INTERVENTION DISCONTINUATION

A subject would be discontinued from the study intervention if a medical condition develops that precludes the continuation of the treatment intervention. For participants who discontinue the RELIEF Study prior to completing all scheduled treatment sessions (regardless of the reason), we will make every attempt to obtain the above-mentioned outcome measurements. If the study participant is unwilling or unable to undergo the laboratory-based tests (e.g., difficulty tolerating the protocol, experienced an adverse event to a lab test) we will still attempt to obtain the clinical outcome measures. In instances where an adverse event does occur, we will follow-up with participants until the event is resolved or until the IRB deems it unnecessary to continue to follow the participant.

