#### **10.3.4 Protocol Deviations**

A checklist of potential protocol deviations will be created and maintained for tracking by the Steering Committee (see appendix). Each protocol violation report will include a description of the violation, the type of deviation that occurred, whether the date the deviation occurred, and whether the IRB was notified. The Steering Committee will review protocol deviations on an as needed basis to determine if subjects should continue in the study, the impact on the procedures, and the next steps for subject continuation. Examples of protocol violations include enrollment of an ineligible subject, randomization of an ineligible subject, failure to collect all screening tests, serious adverse events not reported in a timely fashion, breach of confidentiality, subject lost to follow-up, and visits outside of time window.

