## Appendix: STUDY COMPLETION

*To be completed by study coordinator*

1. Date of final study visit: \_\_\_\_ / \_\_\_\_ / \_\_\_\_  
Day Month Year
2. Participant notified regarding end of active protocol study participation?  
☐ YES ☐ NO
3. Date of last-known study intervention: \_\_\_\_ / \_\_\_\_ / \_\_\_\_  
Day Month Year
4. Primary reason for terminating participation in the study:
  - ☐ Completed study
  - ☐ Not eligible\*
  - ☐ Participant was determined after enrollment to be ineligible (provide comments) \_\_\_\_\_\*
  - ☐ Participant withdrew consent
  - ☐ In the principal investigator's opinion, it was not in the participant's best interest to continue (provide comments) \_\_\_\_\_
  - ☐ Adverse event (If checked, complete the AE form)
  - ☐ Death
  - ☐ Lost to follow-up
  - ☐ Other (specify): \_\_\_\_\_
  - ☐ Unknown

\*If participant determined to be ineligible due to CES-D score, give participant the DEBRIEFING – DEPRESSION letter.

Comments:

Investigator Signature: \_\_\_\_\_

Date: \_\_\_\_\_

DAY-MONTH-YEAR

Participant ID # \_\_\_\_\_

Visit Date \_\_\_\_/\_\_\_\_/\_\_\_\_

---

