## PHYSICAL EXAM - HEALTH STATUS REASSESSMENT

*To be completed by clinician if indicated in Health Status Reassessment*

This participant has self-reported a change in his or her health status and needs to be reassessed for adverse events and ability to participate in the study. Refer to HEALTH STATUS REASSESSMENT form for details and complete the form below based on findings.

| Category                                               | Normal or Abnormal                                                                                            | If abnormal, describe below |
|--------------------------------------------------------|---------------------------------------------------------------------------------------------------------------|-----------------------------|
| General Appearance                                     |  Normal
 Abnormal
 Not Examined |                             |
| Musculoskeletal                                        |  Normal
 Abnormal
 Not Examined |                             |
| Extremities/
Skin                                   |  Normal
 Abnormal
 Not Examined |                             |
| Neurological
(dermatomes,
myotomes,
reflexes) |  Normal
 Abnormal
 Not Examined |                             |
| Other, specify:
_____                               |  Normal
 Abnormal
 Not Examined |                             |

I certify this patient is:

- ☐ Able to continue study
  - ☐ Temporarily unable to continue in the study at this time due to a self-limited medical condition
    - ☐ Reassess health status in \_\_\_\_\_ days / weeks. (complete Protocol Deviation Form and Adverse Event Form)
  - ☐ Unable to continue in the study due to a serious change in medical status (complete Adverse Event Form, Protocol Deviation Form and Study Completion Form)
- ☐ I have recommended the participant seek medical care from his or her personal physician.

Investigator Signature: \_\_\_\_\_

Date: \_\_\_\_\_

DAY-MONTH-YEAR

Participant ID # \_\_\_\_\_

Visit Date \_\_\_\_/\_\_\_\_/\_\_\_\_

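### Section 7.1, the MRI pregnancy rule and the case report forms end study participation, section 8 promises continued outcome follow-up, and nothing says which governs

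*Supplement*

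**What the plan says.** **Texts that end participation**

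- Section 7.1, after a pre-treatment check that finds hard neurological signs or serious systemic disease: "they will be excluded from further participation from the study". The same section calls such a case a dismissal from the protocol. For fever or unexplained weight loss, asked about at Visits 2 to 9, "research participation may be delayed, temporarily discontinued, or permanently suspended at the discretion of the examining clinician".
- Section 6.2.2, Group 1 methods, on the urine pregnancy test: "positive results will exclude a participant from remaining in the study". Section 4.2 lists as an Experiment 1 exclusion "Have a positive result from pregnancy test administered the day of each MRI", so the test recurs at the Visit 8 and Visit 9 scans.
- The clinician's health status reassessment form (Case Report Forms, Final Version 5.0) has a box "Unable to continue in the study due to a serious change in medical status", which calls for a Study Completion form. That form asks for the "Primary reason for terminating participation in the study". The checklists for Visits 2 to 9 ask one question about continuing in the study, and a negative answer leads to the same form.

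**Texts that expect follow-up to go on**

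- Section 8, for those who leave before all scheduled treatments, for any reason: "we will make every attempt to obtain the above-mentioned outcome measurements". A second sentence says clinical outcomes will still be sought from anyone unwilling or unable to do the laboratory tests.
- Section 9.5 includes in the intention-to-treat analysis all randomized participants with at least baseline assessments. An exclusionary condition arising on study removes a participant from the per-protocol set only.

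**The concern.** Stopping a treatment, stopping a laboratory test and stopping outcome collection are three separate decisions. Section 8 and the analysis sets treat them so. Section 7.1, the pregnancy rule and the forms merge them into one. A coordinator with a completed reassessment form would be directed to close the participant out, while section 8 would have the same person telephoned for a pain and a disability score.

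A new hard neurological sign is a deterioration, so scores missing for that reason are likely to be poor ones, and the deterioration might be related to the assigned treatment. If removals were unequal across arms, the primary comparison would shift, and the arm with more removals for worsening would look better than it was.

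**Working it through.** **1. The plan's own figure.** Section 9.2 gives power 0.80 for the RCT component with 54 per arm, d = 0.5 and 10% attrition. Evaluable n = 54 × 0.9 = 48.6 per arm. A two-sample comparison at one-sided 0.05, unadjusted and without gain from the baseline covariate, gives power 0.794, which reproduces it. (Two-sided 0.05 on the same basis gives 0.693; with an assumed baseline correlation of 0.5 it gives 0.812.) If removals pushed total loss to an assumed 12%, 15% or 20%, the one-sided figure would be 0.786, 0.774 or 0.751. Power is therefore not the main issue. The stated simulation assumptions have dropout completely at random, which removal for worsening would not be.

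**2. Who falls under which text.**

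| Event | Text ending participation | Covered by section 8? |
|---|---|---|
| Hard neurological signs or serious systemic disease before a treatment | 7.1, reassessment form | First sentence can be read to cover it, since a treatment is outstanding |
| Fever or weight-loss pathway at Visit 8 or 9 | 7.1 (discretionary), reassessment form | Not by the first sentence once all six treatments are done; only by the lab-test sentence, if it applies |
| Positive pregnancy test at the Visit 8 or 9 scan | 6.2.2 with 4.2 | Lab-test sentence only |

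In no row do the documents state which text prevails.

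**3. What would stand in for a missing score.** The schedule in section 6.1 has the Roland Morris questionnaire (RMDQ) at Visits 1, 2, 8 and 9 only. Someone removed during treatment has only a pre-treatment RMDQ. The pain rating (NPR) is taken at every treatment visit, so its last value would be more recent. Section 9.5 carries the last observation forward when missingness is not significantly related to other factors. With few removals that test would rarely detect a relation, so a baseline RMDQ could be used for someone who had deteriorated.

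**4. Size, on assumptions.** Error in an arm mean = p × w, where p is the share of the arm removed and w is how much worse the true OA3 score is than the value used. The documents give neither, so both are assumed.

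- RMDQ, p = 2% to 10%, w = 3 to 6 points: 0.02 × 3 = 0.06; 0.05 × 6 = 0.30; 0.10 × 6 = 0.60. The upper end is 0.60/3 = 20% of the 3-point important difference.
- NPR, p = 2% to 10%, w = 2 to 4 points: 0.02 × 2 = 0.04; 0.10 × 4 = 0.40, which is 0.40/2 = 20% of the 2-point difference.

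Ten per cent of 54 is 5.4 participants, all removed for worsening in one arm, so the upper end is a severe case. Equal removals in all arms would largely cancel in the contrast.

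**The case against.** The best defence is that section 8 already settles the main case. It speaks of leaving the study, not only the treatment, and covers any reason. The 7.1 neurological check precedes each treatment, so a person excluded there has a session outstanding and falls within section 8. The analysis sets agree, and section 9.5 adds sensitivity analyses for data missing not at random. This stands as a possible reading, and it defeats the inference that the plan discards these scores. It does not show that staff would read it so: 7.1 and the forms say the opposite without referring to section 8.

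A reader might also infer that section 10.3.4 removes participants after deviations. It does not. The Steering Committee reviews deviations as needed "to determine if subjects should continue in the study", which is discretionary.

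A reader might further infer that becoming unfit for any laboratory test ends participation. Only the pregnancy rule says that. A positive migraine screen cancels the TMS test, implanted metal bars the participant from TMS and MRI testing, and other possible contraindications go to the principal investigators.

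The defence is also right that pregnancy removals have no evident route to bias between arms, because arms are randomized within experiment and stratified by sex. At Visit 8 the packet places the pain and disability forms before the laboratory checklist, so a positive test that day need not cost the primary endpoint. However, the health status form comes before both questionnaires in that packet. Finally, the Study Completion form records the last intervention date apart from the final visit date, but no box says that treatment has stopped while follow-up goes on.

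**Conclusion.** The concern holds as an unreconciled contradiction that puts outcome data at risk. It does not hold as a stated loss of data. Section 7.1, the Experiment 1 pregnancy rule and the reassessment and Study Completion forms end participation; section 8 and the intention-to-treat definition expect outcomes to be pursued; precedence is not stated. A removal at Visit 8 or 9 rests on section 8's lab-test sentence alone.

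If 7.1 and the forms are followed literally, OA3 scores may be missing in people removed for worsening. That missingness would be informative, with a baseline RMDQ as a possible substitute. The size is modest: up to about 0.6 RMDQ or 0.4 NPR points in an arm mean, resting wholly on assumed removal rates and score differences. Where baseline is carried forward for someone who worsened, the error hides harm. The contradiction can be removed by wording alone.

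**What to change.** Reconcile section 7.1, sections 6.2.2 and 4.2, and the forms with section 8:

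- State in section 8, with cross-references from the other places, that outcome follow-up applies to every randomized participant unless consent is withdrawn. Include those who stop at or after Visit 7. NPR and RMDQ would be sought at the planned OA3 and OA4 times, by telephone or online if needed.
- On the reassessment form and visit checklists, replace the single continuation item with three: intervention, laboratory testing and clinical outcomes.

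What ends treatment or a laboratory test is for the sponsor and clinicians to decide and is not at issue here. The cost is protocol and form wording plus a little follow-up effort for a few participants.

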## **7.2 Assessing, Recording, and Analyzing Safety Parameters**

All Adverse Events will be reported to the Study Coordinator who will complete an Adverse Event Form and collaborate with study staff involved in the AE. If applicable, the Medical Director will review the AE and determine the Common Terminology Criteria for Adverse Events (CTCAE) scale. The Study Coordinator then compiles masked AE reports for the PIs to review.

Twice monthly, adverse events and serious adverse events will be assessed by the unblinded study coordinator and will be entered directly into REDCap™, an electronic data management system. Potential unanticipated side effects of the manual therapy interventions will be monitored at each study visit and entered by a research assistant. A tracking report will be developed as part of the database to allow the coordinator to assess recruitment, participant status, upcoming visits, and outstanding assessments.

Biannually an AE summary report will be generated and provided to the Independent Monitors for review and forwarded to the IRB and NCCIH.

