## **7.3 Adverse Events and Serious Adverse Events**

An adverse event (AE) is any untoward medical occurrence in a subject during participation in the clinical study or with use of the experimental agent being studied. An adverse finding can include a sign, symptom, abnormal assessment (laboratory test value, vital signs, electrocardiogram finding, etc.), or any combination of these.

A serious adverse event (SAE) is any AE that results in one or more of the following outcomes:

- Death
- A life-threatening event
- Inpatient hospitalization or prolongation of existing hospitalization
- A persistent or significant disability/incapacity
- A congenital anomaly or birth defect
- An important medical event based upon appropriate medical judgment

We will utilize the NCI Common Terminology Criteria for adverse Events which are a descriptive terminology that can be utilized for Adverse Event (AE) reporting and provides a grading (severity) scale for each AE. AEs will be labeled according to severity, which is based on their impact on the patient utilizing the following criteria:

Grade refers to the severity of the AE. The CTCAE displays Grades 1 through 5 with unique clinical descriptions of severity for each AE based on this general guideline:

- Grade 1 Mild; asymptomatic or mild symptoms; clinical or diagnostic observations only; intervention not indicated.
- Grade 2 Moderate; minimal, local or noninvasive intervention indicated; limiting age-appropriate instrumental ADL\*.
- Grade 3 Severe or medically significant but not immediately life-threatening; hospitalization or prolongation of hospitalization indicated; disabling; limiting self care ADL\*\*.
- Grade 4 Life-threatening consequences; urgent intervention indicated.
- Grade 5 Death related to AE.

A Semi-colon indicates 'or' within the description of the grade.

A single dash (-) indicates a grade is not available.

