#### 7.4 Reporting Procedures

SAEs that are unanticipated, serious (Grade 3), and possibly related to the study intervention will be reported to the Independent Monitor(s), IRB, and NCCIH in accordance with requirements.

- Unexpected fatal or life-threatening AEs related to the intervention will be reported to the NCCIH Program Officer and Independent Monitoring Committee within 2 days and to the IRB within 1 day. Other serious and unexpected AEs related to the intervention will be reported to the NCCIH Program Official within 7 days.
- Other anticipated or unrelated SAEs will be handled in a less urgent manner but will be reported to the Independent Monitor(s), IRB, NCCIH, and other oversight organizations in accordance with their requirements. In the annual AE summary, the Independent Monitor(s) Report will state that they have reviewed all AE reports.

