#### **10.3.5 Monitoring**

The Steering Committee will be responsible for study monitoring. This committee will review and approve the study protocol prior to initiation of enrollment, will review SAEs and AEs at least twice annually and will be alerted to any interim concerns. Should any SAEs occur, they will be reported within 24 hours to the PIs.

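### Section 7.2 puts SAEs on a twice-monthly cycle without reference to the expedited reporting clocks, and 7.4 glosses serious as Grade 3 against the outcome-based definition in 7.3

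*Supplement*

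**What the plan says.** On timing, section 7.2 gives two routes. The first is event-driven and has no time limit: "All Adverse Events will be reported to the Study Coordinator who will complete an Adverse Event Form". The second is periodic: "Twice monthly, adverse events and serious adverse events will be assessed by the unblinded study coordinator", and these events are entered into REDCap as part of that step. The same section adds that "Potential unanticipated side effects of the manual therapy interventions will be monitored at each study visit", and section 7.1 says "At visits 2-9 the study staff will use the Health Status Reassessment CRF".

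Section 7.4 sets the external clocks. Unexpected, related events that are fatal or life-threatening go to the NCCIH Program Officer and the "Independent Monitoring Committee within 2 days and to the IRB within 1 day". Other serious, unexpected, related events go to NCCIH within 7 days. Anticipated or unrelated SAEs have no numeric limit. Section 10.3.5 adds an internal clock: "Should any SAEs occur, they will be reported within 24 hours to the PIs".

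On the meaning of serious, section 7.3 says "A serious adverse event (SAE) is any AE that results in one or more of the following outcomes" and then lists death, a life-threatening event, hospitalization, disability, congenital anomaly and important medical event. It gives the CTCAE grade separately, as a measure of severity. The lead sentence of 7.4 nevertheless describes its scope as "SAEs that are unanticipated, serious (Grade 3), and possibly related to the study intervention".

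**The concern.** There are two separate problems.

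First, 7.2 names SAEs in a cycle of about half a month and neither exempts them from it nor points to the shorter limits elsewhere. The 7.4 limits depend on an event having been judged serious, unexpected and related. The only interval that section 7 attaches to assessing SAEs is the twice-monthly one.

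Second, the parenthesis in 7.4 substitutes a severity grade for the seriousness definition. Someone applying it literally would use a different filter from the one in 7.3.

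The stake is safety oversight. Section 9.3 lets the IMC, in consultation with NCCIH, stop the study for excessive SAEs, so the committee depends on receiving them promptly and by one definition. The protocol deviation SOP codes failure to report an SAE within 24 hours as a Category A safety deviation. Staff who took the 7.2 cycle as their timetable for SAEs could therefore commit a deviation that the study itself defines.

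**Working it through.** The plan gives no figure on this point to reproduce, so the check sets the passages side by side.

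**Timing.**

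| Rule | Applies to | Limit |
|---|---|---|
| 7.2, periodic step | AEs and SAEs | twice monthly |
| 7.2, report to coordinator | all AEs | none stated |
| 7.1, health inquiry | visits 2-9 | at the visit |
| 10.3.5 | any SAE, to the PIs | 24 hours |
| 7.4, first bullet | unexpected, related, fatal or life-threatening | IRB 1 day; NCCIH and IMC 2 days |
| 7.4, first bullet | other serious, unexpected, related | NCCIH 7 days |
| 7.4, second bullet | anticipated or unrelated SAEs | none stated |

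A twice-monthly step recurs every 365.25 / 24 = 15.2 days. That is longer than every numeric limit in the table, so the step cannot by itself satisfy any of them. The remaining judgements carry no time limit: grading by the Medical Director where applicable (7.2), attribution by the clinical investigator (7.3) and, for participants dismissed on health grounds, the Medical Safety Committee's causality review (7.1). Section 7.4 does not say whether its clocks run from occurrence or from awareness.

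*Worst case only.* Suppose the periodic step were the sole route, events arose uniformly over the interval L, and the clocks ran from onset. Then P(wait > c) = 1 - c/L. With L = 15.2 days, and 14 to 16 days as an assumed range:

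- c = 1 day: 1 - 1/15.2 = 93% (93% to 94%)
- c = 2 days: 1 - 2/15.2 = 87% (86% to 88%)
- c = 7 days: 1 - 7/15.2 = 54% (50% to 56%)
- mean wait: 15.2/2 = 7.6 days (7 to 8)

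The documents contradict the sole-route premise, so these are upper bounds and not expected rates of late reporting.

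**Meaning of serious.** Taking the Grade 3 parenthesis literally:

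- Grades 4 and 5 fall outside the lead sentence. The first bullet picks up unexpected, related fatal or life-threatening events by outcome, so their 1- and 2-day clocks are intact.
- An SAE graded below 3 falls outside the lead sentence. An important medical event graded 2 is the clearest possibility. If the gloss is carried into the bullet on other serious events, such an event also leaves the 7-day rule.
- The 24-hour rule in 10.3.5 covers any SAE and has no grade filter, so it is unaffected.

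The adverse event form records severity grade and serious status in separate columns, which confirms that the study treats them as different attributes.

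**The case against.** The strongest reply on timing is that the twice-monthly line is housekeeping. It sits beside REDCap entry and tracking reports. The preceding paragraph of 7.2 has every adverse event reported to the coordinator. The health status forms tell staff to alert the coordinator when a change is reported, and marking an event serious on the adverse event form triggers the SAE form. Attribution and grading belong to other people, and nothing makes them wait for the coordinator's review. This stands as far as it goes: a reader might infer that SAEs are assessed only twice a month and that most would miss their limits, and the text supports neither inference. The reply does not reconcile the passages. Section 7.2 still names SAEs in the cycle, and the event-driven routes in section 7 carry no time limit for assessment.

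On the grade, the reply is that the 7.3 guideline for Grade 3 already includes hospitalization, disabling events and medically significant events, so most SAEs that are not fatal or life-threatening would be Grade 3 anyway. That is fair, and it makes an admission for observation a poor example of an event that escapes. The guideline does not make grade and seriousness the same thing, and an SAE below Grade 3 remains possible. The documents do not give the share of such events.

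A completed data and safety monitoring plan is mentioned in 7.6 but not shown. It may hold more detail on timing. It would not remove a contradiction in the protocol that staff work from.

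**Conclusion.** Two contradictions stand. Section 7.2 is not reconciled with 10.3.5 and 7.4 on the timing of SAE assessment. The lead sentence of 7.4 conflicts with the outcome definition in 7.3.

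Their reach is limited. The first leaves it unstated how seriousness, expectedness and relatedness will be judged in time; it is not evidence of a late-reporting rate. The second affects the general reporting sentence and possibly the 7-day rule. A reader might infer that it also loosens the 24-hour, 1-day or 2-day clocks, but those are set by any SAE or by fatal or life-threatening outcome and do not refer to grade.

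No estimand, power figure or error rate is touched. The conclusion rests on the protocol text alone and assumes that the monitoring plan does not override it. The change should be made because it protects expedited safety reporting at almost no cost.

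**What to change.** In 7.4, delete the Grade 3 parenthesis and state that serious means meeting the 7.3 list, whatever the CTCAE grade.

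In 7.2, limit the twice-monthly cycle to non-serious adverse events and to periodic review or data entry. Add that SAEs follow 10.3.5 and 7.4, and that seriousness, expectedness and relatedness are assessed in time to meet those limits.

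In 7.4 and 10.3.5, state the event that starts each clock. Check that the monitoring plan uses the same wording.

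The cost is a few sentences in sections 7 and 10. The existing staff and forms suffice, since the coordinator already receives every report and the adverse event form already separates grade from seriousness.
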